# Outcomes

## Primary outcomes

The study has two primary outcomes: regimen completion and safety

Regimen completion: we have selected regimen completion as one of the two primary outcomes because we consider this to represent a summary measure of tolerability – i.e. the combined impact of patient decision to stop due to symptoms, such as stomach upset, anorexia, or fatigue, and health care provider decision to stop based on objectively measured events such as rash, or liver or hematological toxicity. This outcome has the additional advantages of being easy to define and measure, and does not require the added judgment of investigators, or an outside panel. Treatment completion is also readily comparable to completion measured in other studies.

This outcome will be based on the number of pills dispensed and pill counts during treatment phase follow-up visits. For the 2-month high-dose rifampin regimens, treatment phase medical follow-up visits by patients will be made two weeks after the start of therapy, at 4 weeks, and at end of therapy, and for 4R_10_ after 1 and 2 months and at end of therapy (total 3 follow-up medical visits for each regimen). Completion will be defined as taking 80% of doses within 120% of allowed time (48 doses within 72 days for the two-month regimens, and 96 doses within 144 days for the 4-month regimen).

Safety: Grade 3 to 5 adverse events (and Grade 1-2 rash) which result in permanent discontinuation of the study drug, and that are considered probably or possibly related to the study drug by the majority of a three-member independent and blinded Adverse Events panel. This panel (see below for details on panel) will review all events when the study investigator / primary health care provider stopped the study drug permanently because of their concerns of a potential drug-related adverse event. The panel will review these incidents blinded to rifampin dose, and independently from each other. Grading will be standardized using criteria established by the American Thoracic Society for hepato-toxicity (Saukkonen et al. 2006) and the National Cancer Institute for all other adverse events (National Cancer Institute Terminology Criteria for Adverse Events v4.0, at: <https://evs.nci.nih.gov/ftp1/CTCAE/CTCAE_4.03/Archive/CTCAE_4.0_2009-05-29_QuickReference_8.5x11.pdf>

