# Objectives

### Primary objectives

1) Compare completion of three different regimens of daily self-administered oral rifampin: (1) Standard = 10 mg/kg/day for 4 months (4R_10_), or (2) 20 mg/kg/day for 2 months (2R_20_), or, (3) 30 mg/kg/day for 2 months (2R_30_). Completion will be defined as taking at least 80% of doses in 120% of allowed time (48 doses within 72 days for the 2-month high dose regimens and 96 doses within 144 days for the standard regimen).

2) Compare the three regimens in terms of their rate of Grade 3 to 5 adverse events (AE) that result in permanent discontinuation of study drug and are considered probably or possibly related to the study drug by an independent 3-member adjudication panel blinded to study arm (safety).

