# Design

Three-arm, phase 2b, partially-blind, randomized trial of patients who are recommended to take latent TB therapy. The trial will test superiority of completion and non-inferiority of safety. All members of the same household of a patient with newly diagnosed active pulmonary TB (household contacts) will be randomized together (i.e. cluster randomized). The two higher doses will be administered double-blind. This means that household members will be aware of the duration of their regimen – i.e. whether they are randomized to two months (of high dose 20 or 30 mg/kg/day) or four months (of standard dose 10 mg/kg/day) of treatment. But participants and treating teams will remain blinded to the specific dose (i.e. 20 or 30 mg/kg) for those randomized to the two-month high-dose regimens.

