# Rationale:

We propose a phase 2b trial initially to assess acceptability, tolerability and safety – through the combined outcome of completion, plus a careful assessment of safety through detailed independent review of all Grade 3 or worse adverse events. This trial will have several mechanisms to ensure safety of study participants, including review within 24 hours by the coordinating centre of all adverse events associated with suspension of study drug, subsequent review by an independent panel of all potentially serious drug related adverse events, and periodic as well as ad hoc review of safety data by an independent data safety and monitoring board (DSMB). If this trial demonstrates that higher doses of rifampin are as well tolerated and safe as standard doses of rifampin, and when given for two months have better completion, this will justify a full-scale phase 3 future trial to assess efficacy of these regimens. If the highest dose (30mg/kg/day) is equally well tolerated as the 20mg/kg/day dose, then we will select the highest dose for the phase 3 trial. On the other hand, if the 30mg/kg/day dose is less well tolerated or associated with a higher rate of serious adverse events then we will use the 20mg/kg/day dose in phase 3.

We propose an open label trial for duration – because the difference in duration is the expected key determinant of treatment completion and the short duration of only two months is the major advantage for patients. Since there is a possibility of worse tolerability and safety with higher doses, the difference in duration is necessary to offset any potential disadvantages of the short higher dose regimen. We have used an open label design successfully in previous trials; to overcome potential bias in ascertainment of outcomes we will utilize blinded independent review panels for the outcomes of adverse events and active TB – as we have done in past studies (Diallo et al. 2018; Menzies D et al. 2008; Menzies et al. 2018). We will blind the two higher doses, as we expect that patients and health care providers may be more likely to report side effects with the higher doses, and the duration is the same.

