## Secondary outcomes

1. Grade 1 to 2 adverse events which result in permanent discontinuation of the study drug and are considered probably or possibly related to the study drug by the adverse events panel.
2. Active TB – symptoms will be ascertained monthly by direct questioning during treatment phase follow-up visits, and by telephone call every 3 months up to 26 months after randomization. This allows two years of follow-up after completion of the shorter regimen. Patients with possible active TB will be investigated following a detailed and standardized protocol. The final diagnosis will be established by an independent 3-member Active TB panel who will review all possible TB diagnoses blinded and independently. Active TB will also be determined passively by sending the names of all study participants to the local TB authorities to cross-check their list of all persons notified to have active TB against our list of study participants. (This procedure will be described in participants’ informed consents).

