# Statistical analysis

Primary analyses

The are two planned primary analyses:

1) Superiority of treatment completion: treatment completion is defined as taking at least 80% of the recommended doses within 120% of allowed time. Since this is a dichotomous outcome, this primary analysis will be a logistic regression, using an identity link, and estimated via generalized estimating equations to account for clustering by household. An exchangeable correlation structure and empirical standard errors will be used. We will compare the proportion having treatment completion in each high dose arm against the standard arm – 10 mg/kg/day rifampin given for 4 months.

Given that some exclusion post randomization could occur (for example, contacts are enrolled, but the DST results of their index case were not available at the randomization, then later the DST shows resistance to rifampin), a modified intention to treat analysis will be used – with these valid post-randomization exclusions not included in the primary analysis. A secondary analysis will be done among patients who completed therapy per protocol.

2) Non-inferiority of safety: analysis of grade 3-5 adverse events will be as for relatively rare dichotomous outcomes. Poisson regression will be used to compare the occurrence of the grade 3-5 adverse events between each of the two experimental arms and the conventional arm. To account for clustering by household, we will use Generalized Estimating Equation (GEE), with an exchangeable correlation structure and empirical standard errors. To assess non-inferiority, we will use the confidence interval approach, and compare the upper limit of the difference versus a margin of 4%.

Secondary analyses:

Non-inferiority of completion. A planned secondary analysis will assess non-inferiority of completion. The maximum allowable (maximum tolerated) difference will be **5%, with one-sided significance level.**  With the number of participants we expect to enroll for the primary analysis (1359), we will have 80% power to show non-inferiority if any of the experimental arms has 5% higher completion than the control arm, assuming the completion in control arm will be between 70 and 80 % (as it was in the previous RCT).

- We will compare the occurrence of grade 1-2 adverse events reported by study investigators and judged by the independent blinded adjudication panel to be possibly or probably related to study drug in the same way as grade 3-5 adverse events.

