- Active TB – the incidence of active TB (microbiologically confirmed and all forms) in the 26 months post-randomization per 100 person-years of follow-up will be compared between all three arms.

All analyses will include adjustment for clustering by household. In stratified analysis, results will be presented by indication for LTBI treatment. Sensitivity analyses will be conducted where by analysis are stratified by study centre and by country.

Interim analyses

To optimize protection of safety of study participants, we plan at least two interim analyses of study regimen completion and of Grade 3-5 adverse events. The first analysis will be conducted after the first 150 participants randomized (i.e. approximately 50 in each arm) have completed therapy. This means we will assess outcomes that have occurred in each of these individuals up to 146 days post-randomization. The second interim analysis will be conducted 146 days after randomization of the 450^th^ Participant – i.e. after approximately 150 participants should have completed therapy in all 3 arms. However, as described below, the 2^nd^ analysis may be performed sooner if there are concerns about excess toxicity with either high-dose arm.

Our goal is to identify as early as possible if the high dose rifampin regimens are associated with a clinically important increased rate Grade 3-5 AE, or intolerance – defined as failure to complete therapy. The study bio-statistician will conduct both interim analyses in a blinded fashion. Given that there are two planned interim analyses, the p value -adapted for multiplicity of testing- that will be used to consider significant the difference between proportions is of p<0.022 (Pocock’s method).The Data Safety and Monitoring Board (DSMB – see below for more details) will also consider results while remaining blinded to the identity of the regimens. For each interim analysis, if any of the regimens meets criteria for a clinically important difference in adverse events or completion, then we will unblind in step-wise fashion. If unblinding is deemed necessary, the person in charge of code breaking will be the principal investigator ([name]) and the study coordinator ([name]). Same procedures will be followed if DSMB asks for unblinding in specific cases for serious and unexpected adverse events.

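### A related Grade 3-5 event first found at or after the last dose can enter no named safety outcome, and its reporting is left to case-by-case decisions

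*Protocol*

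**What the plan says.** **Outcome definitions.** Under Primary objectives, the safety outcome is the rate of "Grade 3 to 5 adverse events (AE) that result in permanent discontinuation of study drug" that the blinded panel judges possibly or probably related. Primary outcomes repeats the condition and adds Grade 1-2 rash. The only other adverse-event outcome, under Secondary outcomes, is "Grade 1 to 2 adverse events which result in permanent discontinuation of the study drug", again judged related.

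**What is collected.** Methods to ensure the safety of study participants runs ascertainment to 30 days after the end of treatment. For events after treatment, the site investigator and the coordinating center decide case by case what to investigate and report. On treatment, a Grade 3-4 event considered possibly or probably related requires a permanent stop. An initial report is required for every event of Grade 3 or higher, including those that do not call for stopping the drug.

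**What the panel sees.** Primary outcomes says the panel "will review all events when the study investigator / primary health care provider stopped the study drug permanently because of their concerns". Rationale promises "careful assessment of safety through detailed independent review of all Grade 3 or worse adverse events" and then "subsequent review by an independent panel of all potentially serious drug related adverse events". The safety section and the section on adjudication panels send final reports to the panel and name no stop condition.

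**Blinding.** Participants and staff know whether the course is two or four months. Within the two-month arms, "participants and treating teams will remain blinded to the specific dose".

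**The concern.** Rationale relies on blinded panels to offset the open-label comparison of durations. The stop decision comes before the panel step and is made by people who know the duration. If an event can count only when the drug was stopped, two kinds of related event may fall outside the outcome:

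- **Events first found at or after the last dose.** No drug remains to be stopped, so the condition cannot be met. Whether such an event is even reported is a local, duration-aware decision.
- **On-treatment Grade 3-4 events with the drug kept or restarted.** The site has explained the event in some other way, but the panel might have called it possibly related.

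The safety comparison helps decide whether phase 3 goes ahead and at which dose. The first kind also interacts with the design, because the two-month arms reach the uncountable period 60 days sooner than 4R10 does.

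**Working it through.** **1. The plan's own safety figure.** Table 3 gives 234 per arm for 1% v 2% with a 4-point margin. Inputs: household size 4 and ICC 0.05, so the design effect is 1 + (4 - 1) x 0.05 = 1.15. With one-sided alpha 0.05 and 80% power:

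n = (1.645 + 0.842)^2 x (0.01 x 0.99 + 0.02 x 0.98) / (0.04 - 0.01)^2 x 1.15, which rounds up to 234.

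For 2% v 3% the same formula gives 385 against the stated 386. Table 3 holds, and the point here is not about sample size.

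**2. Can a post-treatment event count?** The condition is that the event leads to permanent discontinuation. After a completed course there is nothing to discontinue. An event that itself caused the stop and was confirmed later still counts.

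| Days since first dose (course taken on schedule) | Two-month arms | 4R10 |
| --- | --- | --- |
| 1-60 | can count | can count |
| 61-90 | followed, cannot count | can count |
| 91-120 | not followed | can count |
| 121-150 | not followed | followed, cannot count |

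The uncountable period is 30 days in every arm. As a share of the follow-up window it is 30/(60 + 30) = 33% on two months and 30/(120 + 30) = 20% on four.

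**3. How wide is the drug-kept route?** A Grade 3-4 event considered even possibly related must lead to a permanent stop. What remains is mainly site-panel disagreement in one direction: the site explains the event otherwise and the panel does not. Table S7 shows the opposite disagreement. In adults, 93 - 68 = 25 of 93 stops on 4R (26.9%) and 179 - 131 = 48 of 179 on 9H (26.8%) were not judged related. Providers stopped more readily than the panel attributed, about equally in both arms. Kept-drug events that a panel would have called related are not reported.

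**4. Scale.** Take 412 analysed per arm.

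- One event: 100/412 = 0.24 points.
- The margin: 0.04 x 412 = 16.5 events.
- Expected counts at 2% v 3%: 8.2 and 12.4.
- Standard error at 2% v 3%: sqrt((0.02 x 0.98 + 0.03 x 0.97)/(412/1.15)) = 1.17 points.

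The documents give no number of uncounted events. As an assumption only, 0 to 4 in one arm would shift the difference by 0 to 0.97 points, or 0 to 0.97/1.17 = 0.83 standard errors. The shift is downward if they are lost in a high-dose arm and upward if lost on 4R10.

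**5. Direction.** The high-dose arms have an extra blood test at two weeks, and Rationale expects readier reporting of side effects at higher doses. Both point to more capture there, which is conservative. The earlier end of treatment points the other way. No routine bloods are planned after one month in any arm, so few laboratory events may be found late.

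**The case against.** The case against is substantial.

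- **The endpoint is deliberate.** Both definitions of the primary outcome carry the stop condition. Appendix 2 describes the same condition in the prior 4R trials, which supply the 1-2% benchmark. This stands, and it is why the primary outcome and margin should not change.
- **A supportive table belongs in the SAP, which is not shown.** True of the table. The reporting rule and the panel's remit are protocol procedures, however, and no SAP can recover an event that was never reported.
- **The drug-kept route is nearly closed.** The mandatory stop does most of this. The written exception, for mild rash or an alternate explanation, is illustrated only with rash. This stands.
- **The post-treatment window is 30 days in every arm.** Correct, so the 33% and 20% shares do not by themselves show a difference between arms.
- **Other safeguards exist.** The DSMB reviews unexpected Grade 3-4 events, expected serious events enter all safety analyses, and post-treatment calls ask about hospitalization. These make the events less invisible but place them in no named outcome.

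A reader might infer that the protocol contradicts itself on the panel, so that kept-drug events never reach it. The documents do not support that: Primary outcomes does not say the panel reviews only permanent stops, and the later sections apply no such filter. The wording is narrower in one place than in others, which is an inconsistency and not a proven conflict.

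A reader might also infer that the analysis uses a different outcome, because Statistical analysis says "Poisson regression will be used to compare the occurrence of the grade 3-5 adverse events between each of the two experimental arms" and "we plan at least two interim analyses of study regimen completion and of Grade 3-5 adverse events" without the stop condition. That text is better read as shorthand for the outcome already defined.

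**Conclusion.** The point holds as a low-cost improvement. A panel-related Grade 3-5 event first found at or after the last dose can enter no named outcome, and its reporting is discretionary even though follow-up runs for 30 days. The on-treatment route is narrow.

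Direction and size are unknown, and the effect is probably small. One event is 0.24 points, and the 0 to 0.97 point range rests on an assumed 0 to 4 events. It would be tempting to conclude that the design biases the trial towards a false finding of non-inferiority. The documents give no share of uncounted events and no direction, so no such error rate can be derived from them.

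**What to change.** Keep the primary outcome, the 4-point margin and the sample size. Then:

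1. In Methods to ensure the safety of study participants, make reporting of Grade 3-5 events mandatory through 30 days after the last dose in all arms.
2. In Primary outcomes, state that the blinded panel reviews every Grade 3-5 report whatever was decided about the drug, in line with the safety section. Bring the two phrases in Rationale into agreement with it.
3. Add one supportive comparison of panel-judged possibly or probably related Grade 3-5 events regardless of discontinuation. Give the risk difference and confidence interval for each high-dose arm against 4R10, with no formal margin, and show it to the DSMB beside the primary count at the interim analyses.

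The cost is a few more reports and panel reviews, and one more table. On-treatment Grade 3 or higher reports are already required, so only the post-treatment ones become newly mandatory.

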## Secondary outcomes

1. Grade 1 to 2 adverse events which result in permanent discontinuation of the study drug and are considered probably or possibly related to the study drug by the adverse events panel.
2. Active TB – symptoms will be ascertained monthly by direct questioning during treatment phase follow-up visits, and by telephone call every 3 months up to 26 months after randomization. This allows two years of follow-up after completion of the shorter regimen. Patients with possible active TB will be investigated following a detailed and standardized protocol. The final diagnosis will be established by an independent 3-member Active TB panel who will review all possible TB diagnoses blinded and independently. Active TB will also be determined passively by sending the names of all study participants to the local TB authorities to cross-check their list of all persons notified to have active TB against our list of study participants. (This procedure will be described in participants’ informed consents).

# Trial procedures

## Intervention arms:

Arm 1: 60 doses daily self-administered rifampin at 20 mg/kg (**2R_20_** – maximum 1200 mg/day).

Arm 2: 60 doses daily self-administered rifampin at 30 mg/Kg (**2R_30_**) - maximum 1800 mg/day).

## Comparator:

Arm 3 (standard): 120 doses daily self-administered rifampin at a dose of 10mg per kg per day (4R_10_maximum 600mg per day).

For Canadian sites, the study formulations of rifampicin 20 mg/kg and 30 mg/kg, will be procured by each site, purchased from marketed rifampin capsules (Valeant Canada or Sanofi-Aventis Canada), with dose adjustment, packaging and coding provided by another supplier (Pharmacie [name], [name], Montreal, QC). Formulations of standard dose of rifampicin 10 mg/kg, will be procured in the usual manner as for standard of care in each site in Canada.

For Indonesia rifampin for all study arms, will be purchased from an Indonesian supplier ([name], Indonesia). Because this supplier provides Rifampin in capsules of 300mg and 450mg, there will be no need for re-compounding.

For Vietnam, rifampin for high dose arms will pre purchased from Svizera Europe B.V. ([name], The Netherlands) and rifampin for standard arm from Mekophar Chemical Pharmaceutical Joint Stock Company ([name]), Vietnam.

## Accountability procedures for investigational and comparator drugs:

For intervention arms (high dose arms) in Canadian site: the drugs for the two experimental arms, will be purchased as ROFACT 300mg (DIN 00343617), or RIFADIN 300mg (DIN [02092808](https://health-products.canada.ca/dpd-bdpp/info.do?lang=en&code=19034)). The capsules will be shipped with secure courier to the re-compounding pharmacy ([name], Pharmacie Frayne & associés, [name], [[contact]](https://www.google.com/search?client=firefox-b-d&channel=crow&q=[name]+pharmacy&spell=1&sa=X&ved=0ahUKEwiGpOCj9t7iAhXGV98KHfNyDIUQBQgtKAA&biw=1280&bih=608)) in Montreal. The blind, re-compounded capsules of 300mg and 450mg strength will then be shipped, also by secure courier, to the study site pharmacies in bottles. The labels for each bottle will specify if this contains the 300mg or the 450mg capsules. Each capsule (of 300mg and 450mg) will look the same, for blinding purposes and will not have anything written on it. At each site, for each participant randomized to the high dose arms, the pharmacist, or another health professional designated by the site qualified investigator, will be unblinded. This unblinded pharmacist (or health professional as above) will prepare a bottle with the number of doses needed for that participant until the next planned treatment phase follow-up visit. The bottle given to the participant will be labeled with their (participant’s) name, study ID, and a code corresponding to the arm to which participant has been randomized to. The code that identified each study arm will be known only to the pharmacist (or other designated health professional as above) at each site, designated to prepare the bottles for the participants. The code will also be known to the central study coordinator. This will ensure that the participant and his/her treating team will remain blinded.

At each visit, participants will bring their pill bottles, so that any remaining pills can be counted. Bottles will be refilled with doses needed until the next planned visit. The pharmacy at the site will keep a log of drug dispensed to participants, linking the content of the bottles prepared for each participant to the original bottle received from [name] pharmacy.

In Indonesia and Vietnam the same procedures will be used except that study drugs will be provided directly by Indofarma (for Indonesia) and from Svizera Europa B.V. (for Vietnam), as 300mg and 450mg capsules, with no need for re-compounding before use. The capsules of 300mg and 450mg will look the same for blinding purposes. At each site there will be a person in charge of keeping the codes for the blind arms, who will use the code received at randomization, to prepare the study drug supply until the next planned study visit.

For standard dose (comparator) arm: participants who are randomized to be in the control arm will be provided rifampin at the daily dose specified in the protocol, based on their body weight (10 mg/kg/day, 600mg maximum per day). In Canadian sites, the capsules of rifampin needed will be procured and provided to participants as per standard care. In Indonesia capsules of rifampin for standard arm will be procured from Indofarma and in Vietnam from Mekophar.

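### The arm-level code on each high-dose participant's bottle means that one dose becoming known at a site could reveal 20 versus 30 mg/kg for the site's other high-dose participants

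*Protocol*

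**What the plan says.** The Design section makes the two high doses double-blind: participants and treating teams know the duration but not whether the dose is 20 or 30 mg/kg. The Rationale section explains that patients and providers are expected to report side effects more readily at higher doses.

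Under Accountability procedures for investigational and comparator drugs, an unblinded pharmacist or designated health professional prepares the participant's bottle. It carries the name, the study ID and "a code corresponding to the arm to which participant has been randomized to". The protocol then states: "The code that identified each study arm will be known only to the pharmacist" (or that designee), and adds the central study coordinator. For Indonesia and Vietnam it describes "a person in charge of keeping the codes for the blind arms, who will use the code received at randomization". On handling, it says: "At each visit, participants will bring their pill bottles, so that any remaining pills can be counted". The During treatment section likewise asks participants to bring their medication to all visits.

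On unblinding, Statistical analysis (Interim analyses) assigns code-breaking to the principal investigator and the study coordinator, and continues: "Same procedures will be followed if DSMB asks for unblinding in specific cases for serious and unexpected adverse events". The same section provides for stopping enrolment to the 30 mg/kg arm if that arm alone shows excess events.

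**The concern.** A blind is robust when breaking it for one person tells nobody anything about the next. A label shared by everyone in an arm lacks that property. Anyone who sees the bottles can sort a site's high-dose participants into two groups, and one known dose then names both groups.

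What is at stake is the comparison of 20 with 30 mg/kg. The decision to stop the drug is made by the participant or the treating team, who are the people the blind is meant to cover, and it feeds both completion and the safety outcome. According to the Rationale section, the relative tolerability of the two doses determines which one goes into phase 3. If knowledge of dose changes how readily symptoms are reported or drug is stopped, that choice is affected.

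**Working it through.** The protocol gives no figure on this point, so there is none to reproduce. The check is a reading of the text plus simple arithmetic.

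**1. Level of the code.** The Canadian text ties the code to the arm twice, in the label description and in the sentence on who knows it. The text for Indonesia and Vietnam refers to codes for the blind arms. No participant-level code, kit number or set of several codes per arm is described. The natural reading is one code per high-dose arm, hence two codes. Whether they differ between sites is not stated.

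**2. Does anything else on the bottle separate the doses?** The 300 mg and 450 mg capsules look alike. Assuming the 20 mg/kg arm is filled with 300 mg capsules and the 30 mg/kg arm with 450 mg capsules, capsules per dose are:

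- 20 mg/kg: weight × 20 / 300 = weight / 15
- 30 mg/kg: weight × 30 / 450 = weight / 15

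At 45 kg this is 3 and 3; at 60 kg, 4 and 4; at the maximum doses, 1200/300 = 4 and 1800/450 = 4. On that assumption, the arm code is the only described feature of the bottle that distinguishes the doses.

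**3. Who sees it.** Participants hold the bottle and bring it to every visit. The COVID-19 section indicates that the research team normally does the in-person count. That the treating team also sees it is plausible but not stated.

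**4. How one dose could become known at a site.**

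- A leak or error involving any one participant.
- Stopping enrolment to the 30 mg/kg arm. Interim results and DSMB recommendations go to the trial steering committee, which takes the final decision and includes the qualified investigators of all six sites (Study committees). The code no longer issued is then identifiable as 30 mg/kg. New high-dose participants would be known to receive 20 mg/kg under any labelling. What the shared code adds is exposure of those already randomised and still on treatment.

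**5. Upper bounds.** Sample size considerations gives 453 per arm × 3 = 1359, which implies equal allocation, so 2/3 of participants are in the high-dose arms:

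| Site | Planned | × 2/3 |
|---|---|---|
| Bandung | 500 | 333 |
| Ho Chi Minh City | 450 | 300 |
| Greater Vancouver | 150 | 100 |
| Calgary, Edmonton, Montreal | 100 each | 67 each |

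The site targets sum to 1400 while enrolment closes at 1359. Scaling by 1359/1400 gives 324, 291, 97 and 65.

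**6. How many are on treatment at one time.** The accrual period is not given. If Bandung enrolled evenly over 1 to 4 years (an assumption), the number on a 2-month high-dose course would be 333 × 2/12 ≈ 56 down to 333 × 2/48 ≈ 14. After a leak, those still to enrol are added.

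**The case against.** **One code per arm is inferred.** A code corresponding to an arm need not be the only one, and a code received at randomisation could be issued per participant. That is possible, but the protocol calls it the code that identified each arm and describes nothing finer. If participant-level codes are used in practice, the text should say so.

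**The key is restricted, and DSMB unblinding does not reach the site.** A reader might infer that any single-case unblinding asked for by the DSMB exposes a whole site. The documents do not support that: the described procedure reveals arms stepwise to the DSMB, and nothing in it informs the treating team. The restriction does not, however, prevent inference from the label once a dose is known by another route.

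**Not everyone at a site is at risk.** This stands. Completion is judged by day 72, so participants who have finished treatment cannot have their completion or drug-stopping changed by a later disclosure. The site totals would apply only if disclosure preceded the first participant. A reader might also extend the figure to 2 × 453 = 906, but that needs codes common to all sites, which the protocol does not state.

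**Staff could guess the dose from side effects by code.** This is speculative. The safety section expects side effects similar in nature to the standard dose and reports similar frequency in earlier studies. At the 1% to 3% serious event rates considered for the standard arm, about 167 participants per arm at Bandung would yield roughly 2 to 5 events, too few to tell the arms apart reliably.

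**The primary analyses are largely untouched.** Each high-dose arm is compared with the standard arm, and duration is open by design. Event severity and attribution are judged by a blinded panel. This limits the consequence to 20 versus 30 mg/kg but does not remove it: completion is not adjudicated, and the panel reviews events for which the drug has already been stopped.

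**Conclusion.** The labelling, as written, is weaker than the blind it serves. If one participant's dose becomes known at a site, the shared code can carry that knowledge to the site's other high-dose participants. The result is a conditional risk of differential reporting and stopping between 20 and 30 mg/kg among those on treatment or yet to enrol, with a bearing on the phase 3 dose choice. It is not evidence that the blind will fail or that the comparisons with the standard arm are compromised by the label.

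The upper bounds are about 333, 300, 100 and 67 (three sites) high-dose participants per site. They assume equal allocation, planned site numbers, one code per high-dose arm at each site, and disclosure before enrolment begins there. The realistic number is smaller and depends on timing. The size of any bias cannot be derived from the protocol.

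**What to change.** Take the arm code off the participant's bottle. Label it with the study ID, which is already there, or with a unique dispensing number per participant or household. Keep the list linking ID to arm only with the unblinded pharmacist or designee and the central coordinator, and state that the same rule applies in Canada, Indonesia and Vietnam. A code-break then reveals one participant, or one household where members were randomised together.

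The cost is revised wording for the label and dispensing log and, if a dispensing number is preferred, one field in the existing web system. No extra staff, visits or participants are needed. The small downside is that the pharmacist looks up each ID instead of reading an arm code.
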